## Abstract

**Background:**

In resource-poor areas of China and India, the cardiovascular disease burden is high, but availability of and access to quality healthcare is limited. Establishing a management scheme that utilizes the local infrastructure and builds healthcare capacity is essential for cardiovascular disease prevention and management. The study aims to develop, implement, and evaluate the feasibility and effectiveness of a simplified, evidence-based cardiovascular management program delivered by community healthcare workers in resource-constrained areas in Tibet, China and Haryana, India.

**Methods/design:**

This yearlong cluster-randomized controlled trial will be conducted in 20 villages in Tibet and 20 villages in Haryana. Randomization of villages to usual care or intervention will be stratified by country. High cardiovascular disease risk individuals (aged 40 years or older, history of heart disease, stroke, diabetes, or measured systolic blood pressure of 160 mmHg or higher) will be screened at baseline. Community health workers in the intervention villages will be trained to manage and follow up high-risk patients on a monthly basis following a simplified ‘2 + 2’ intervention model involving two lifestyle recommendations and the appropriate prescription of two medications. A customized electronic decision support system based on the intervention strategy will be developed to assist the community health workers with patient management. Baseline and follow-up surveys will be conducted in a standardized fashion in all villages. The primary outcome will be the net difference between-group in the proportion of high-risk patients taking antihypertensive medication pre- and post-intervention. Secondary outcomes will include the proportion of patients taking aspirin and changes in blood pressure. Process and economic evaluations will also be conducted.

**Discussion:**

To our knowledge, this will be the first study to evaluate the effect of a simplified management program delivered by community health workers with the help of electronic decision support system on improving the health of high cardiovascular disease risk patients. If effective, this intervention strategy can serve as a model that can be implemented, where applicable, in rural China, India, and other resource-constrained areas.

**Trial registration:**

The trial was registered in the clinicaltrials.gov database on 30 December, 2011 and the registration number is
NCT01503814.

## Background

An estimated 17 million people die of cardiovascular disease (CVD) each year with over 80% of these deaths occurring in low and middle-income countries
[1]. Resource-poor areas in China and India, where CVD is already the leading cause of death, confront a rising disease burden with a strained healthcare system often inadequately equipped to deal with these problems
[2–4]. Many of the risk factors strongly associated with CVD, including high blood pressure, tobacco use, and poor diet are among the top risk behaviors in these countries
[5, 6]. For example, in studies assessing hypertension in rural areas of Tibet, China, up to 14.9% of the population aged 15 years or older was found to be hypertensive, with some townships having rates as high as 55.9% in adults 40 years old and above
[7, 8]. The overall hypertension rate was found to be just as high in Haryana, India, with the urban slums of Faridabad District, Haryana similarly affected at 16.5%
[9, 10]. Despite these high rates of hypertension, the number of patients receiving antihypertensive therapy in these areas remains low, and way below the averages seen in urban areas
[7, 11].

There are many well-established interventions such as lifestyle modification of known risk factors and effective, low-cost medications that can help avert the CVD burden in these economic and healthcare resource limited settings
[12–21]. One particularly cost-effective approach is to identify and manage individuals at high cardiovascular disease risk in order to prevent or delay events
[22–28]. This method has been applied and implemented in the Rural Andhra Pradesh Cardiovascular Prevention Study in India and the China Rural Health Initiative in northern China
[29–31].

Community Health Workers (CHWs) are the members who received basic professional training to provide health and medical care for the community. Involvement of CHWs in disadvantaged populations has resulted in a significant improvement in accessing healthcare facilities, screening disease, monitoring community members’ health status and adherence to treatment
[32–35]. Task-shifting to CHWs has been proven as a cost-effective and sustainable approach in chronic disease prevention and control, particularly in those areas with limited economic and healthcare resources
[36]. More recently, with the aid of mobile phones, studies have shown a significant reduction in CHW training time, disease screening time and an enhanced user satisfaction
[37]. A recent systematic review also shows that mobile phone based technology in low and middle income countries positively impacts the chronic disease management and its associated clinical outcomes
[38].

Simplifying and extending the high-risk intervention strategy to suit areas with high CVD burden, but more limited economic and healthcare resources will be essential to addressing this problem in an effective and affordable way in these areas. China and India are two largest developing countries in the world that face similar challenges in terms of the burden of CVD and resource constraints in tackling these challenges. Yet, there are also many differences in the healthcare systems, socio-economical environment and ethno-cultural customs that will make conducting a joint study illuminating and fruitful.

Therefore, we have designed a study to develop and evaluate the effects of implementing, in resource-scarce settings, a highly **sim**plified but guideline-based program for **card**iovascular management by CHWs with the aid of electronic decision support system in rural China and India (the SimCard study). This paper describes the research design and the rationale of the study.

## Methods/design

The SimCard study is a cluster-randomized controlled interventional trial to be conducted in rural areas of Tibet, China and Haryana, India. The design, implementation and reporting of the study follow recommendations from CONSORT statement on cluster-randomized trials
[39]. The trial was registered in the clinicaltrials.gov database on 30 December, 2011 and the registration number is NCT01503814. The study protocol received ethics approval from the institutional review boards at Peking University Health Sciences Center, China, the Public Health Foundation of India, India, and Duke University, USA. Informed consent will be obtained from each study participant.

### Study sites

Two counties in the Tibet autonomous region located in Southwest China – Gongbujiangda and Linzhou - and one tehsil - Ballabgarh in Faridabad District from Haryana State in northwestern India will participate in the study. Villages from these locations will be selected to take part in this study based on the site selection criteria of (1) high CVD burden, (2) limited healthcare resources, (3) having available existing CHWs or qualified candidates who can be trained to fulfill that role, and (4) local government support. A total of 40 villages will be recruited across the two countries, 20 in each country.

### Randomization

In each country, villages will be randomized to receive the intervention or usual care. Randomization will be stratified by country. In China, all selected villages will be randomized by a 1:1 ratio to the intervention and control group with stratification by county and township (the administrative unit managing the villages). In India, randomization will not be stratified by any geographical locations. Randomization in both countries will be conducted by a study staff not involved in the intervention through a central computerized process. Group allocation will be concealed until after the baseline data collection is completed.

### Study population

Participants at CVD high risk will be eligible for study enrollment. In this study, ‘high-risk’ is defined as older age (40 years old and above) with a history of any of the following conditions: coronary heart disease, stroke (ischemic, hemorrhagic, or unknown/unspecified type), diabetes mellitus, and/or having a systolic blood pressure ≥160 mmHg at two different time points measured in the same day during the baseline survey.

Exclusion criteria include having CVD-related complications that cannot be managed in a primary care setting, having a malignancy or life-threatening disease; individuals who are bed-ridden, currently participating in any other clinical trials, unable to stay in the village longer than 8 months in a year, and planning to move in the next year.

### Screening

Before the start of the baseline data collection, a survey will be conducted in all participating villages to screen for high-risk individuals. All village residents 40 years and above will be invited to participate in the survey, which will include a brief questionnaire on disease history and measuring blood pressure twice. All high-risk individuals screened out through this process according to the definition described above, a target minimum of 50 in each village, will be invited to participate in the study.

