#### Systematic training of local CHWs

Enhancing the capacity of local CHWs through systematic training is a key feature of the intervention model. Training of local CHWs in the intervention group will consist of an initial training on the intervention protocol, including education on the targeted CVD lifestyle risk factors and the medications being utilized, followed by refresher training about 1–3 months after the intervention begins. Only CHWs who pass the initial evaluation examination can take part in implementing the intervention. After the training, CHWs will be provided with a list of high-risk individuals screened out at baseline for them to contact and manage according to the protocol.

In Tibet, China, "village doctors" who are not physicians but have basic professional training and can prescribe medications will be chosen to be the CHWs to implement this management plan. In rural India, local women will be recruited and trained to be the study’s CHWs. Because the Indian CHWs have no prior medical experience, they will be partnered with licensed physicians from nearby primary health care centers who are responsible for the prescription duties based on the CHWs’ regular assessments of their assigned high-risk patients.

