### Outcome evaluation

#### Baseline and post-intervention survey

The outcome evaluation for this study will be derived from data collected from the baseline survey and post-intervention follow-up survey of all eligible and consenting high-risk patients in the intervention and control villages. Both survey questionnaires will be identical, and include information on patient’s demographics, disease history, lifestyle behaviors, medication use, primary healthcare services utilization, hospitalizations, and medical care related expenses in the past year. Height, weight, waist circumference, and blood pressure will be measured at that time of the survey. Surveys in both countries will be conducted by trained personnel according to the same standardized operating procedures. The questionnaires used in China and India will be kept nearly identical except for a few variations to fit the cultural context and target the specific lifestyles of the two peoples in these countries such as different types of tobacco use (See Table 
1 for survey indicators).

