### Statistical analysis

All analyses will be conducted at individual level according to intention-to-treat principles, and take into account the stratification design and cluster effects. For the primary outcome, anti-hypertensive medication use, log-binomial models with random effects for villages to account for clustering and random effects for intercept to account for the pre-post correlations within individuals and a fixed effect for country to account for the stratified study design will be used. Other than the main effect from intervention and time, an interaction term between intervention and time will be added in the model to test if the slope of the pre-post changes differs by intervention or control group. To account for the heterogeneity between two countries, the two-way interaction of the country variable with intervention and time will be included into the above models. In the case of significant interaction existing, the separate analysis by country will be conducted afterward. The net effect from intervention will be reported as difference-in-difference of proportions together with model-based 95% confidence intervals obtained by transforming back from models. For continuous outcomes, such as systolic blood pressure, similar strategies will be adopted but linear models instead of log-binomial models will be used. Some adjusted analysis will also be performed to account for potential unbalanced baseline information. Other pre-specified subgroup will include analyses by sex and age (40–59 vs. 60 years or older) using similar strategy for the country variable.

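### The SBP model is in effect a change score; adjusting for SBP measured before allocation would be a modest, almost free precision gain, once the timing of screening is reconciled

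*Protocol article*

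**What the plan says.** On timing, the Screening section reads: "Before the start of the baseline data collection, a survey will be conducted in all participating villages to screen for high-risk individuals". That survey is offered to residents aged 40 and over, "which will include a brief questionnaire on disease history and measuring blood pressure twice". Of the baseline and follow-up surveys, the Outcome evaluation section says: "Height, weight, waist circumference, and blood pressure will be measured at that time of the survey". The Randomization section adds: "Group allocation will be concealed until after the baseline data collection is completed". On these passages, screening and baseline SBP both precede knowledge of allocation.

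Three other places put screening elsewhere. Study population takes the qualifying SBP readings "at two different time points measured in the same day during the baseline survey". The Abstract says that high-risk individuals "will be screened at baseline". The section on training of community health workers refers to "a list of high-risk individuals screened out at baseline".

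On analysis, the Statistical analysis section fits intervention, time and their interaction, with random effects for village and person, to the primary outcome. It then states: "For continuous outcomes, such as systolic blood pressure, similar strategies will be adopted but linear models instead of log-binomial models will be used". It also promises some adjusted analyses for baseline imbalance, without naming covariates. The Sample size section claims more than 90% power for a 3 mmHg net SBP difference at ICC 0.01 and at ICC 0.02.

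**The concern.** With one pre and one post value per person, a random intercept and a free main effect of arm, the intervention-by-time term is, for complete pairs, the difference between arms in mean change. A change score subtracts the whole baseline value, including its day-to-day noise. A model of follow-up SBP on arm with baseline SBP as covariate weights that value by how well it predicts follow-up, and so has a smaller residual variance whenever the pre-post correlation is below 1 and the variances are similar. A reading from a second pre-allocation occasion would improve the prediction further.

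At stake is the precision of the only secondary outcome for which the article states a power. The primary outcome, antihypertensive use, is not affected.

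**Working it through.** **Inputs from the Sample size section.** 20 villages per arm, 50 people per village, SD of change 15 mmHg (variance 225), difference 3 mmHg, two-sided alpha 0.05, ICC 0.01 or 0.02.

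**Formula.** With person-level residual variance v, and the village variance held at the plan's value of ICC × 225:

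SE² = 2 × [ICC × 225 + (1 − ICC) × v / 50] / 20, and power = Φ(3/SE − 1.96).

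**The plan's own figure (v = 225).**

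- ICC 0.01: SE² = 2 × (2.25 + 4.455)/20 = 0.6705, SE = 0.819, power = Φ(1.70) = 95.6%.
- ICC 0.02: SE² = 2 × (4.50 + 4.41)/20 = 0.891, SE = 0.944, power = Φ(1.22) = 88.8%.

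The first matches the stated figure. The second falls marginally short of it.

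**Adjusted analyses, closed form.** The article gives no pre-post correlation ρ, so 0.3 to 0.8 is assumed, with visits exchangeable and the SD of change fixed at 15. Then v = 112.5 × (1 + ρ) with baseline SBP as covariate, and v = 112.5 × (1 + 2ρ)/(1 + ρ) with baseline and screening SBP. At ICC 0.02:

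| ρ | v, baseline | v, both | SE, baseline | SE, both | Power, baseline | Power, both |
|---|---|---|---|---|---|---|
| 0.3 | 146.2 | 138.5 | 0.858 | 0.849 | 93.8% | 94.2% |
| 0.5 | 168.8 | 150.0 | 0.884 | 0.863 | 92.4% | 93.6% |
| 0.8 | 202.5 | 162.5 | 0.920 | 0.877 | 90.3% | 92.8% |

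**Allowing for selection.** Some participants enter because both screening readings are at least 160, which truncates the screening value. Simulation was used to allow for this. The first three rows assume residents' mean SBP 140, the between-person SD shown, reading SD 4 and visit-level SD 15/√2. The last row assumes mean 138, between-person SD 18, day-to-day SD 7.5, reading SD 5, extra follow-up SD 9 and a qualifying history in 15% of residents, rescaled to an SD of change of 15. At ICC 0.02:

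| Scenario | v, baseline | v, both | SE, baseline | SE, both | SE cut | Power, baseline | Power, both |
|---|---|---|---|---|---|---|---|
| SD 12, all enter by SBP | 157 | 152 | 0.870 | 0.865 | 0.6% | 93.1% | 93.4% |
| SD 16, 30% of participants enter by history | 193 | 159 | 0.910 | 0.873 | 4.1% | 90.9% | 93.0% |
| SD 20, 70% of participants enter by history | 205 | 164 | 0.923 | 0.878 | 4.8% | 90.2% | 92.7% |
| Extra follow-up variation | 215 | 186 | 0.934 | 0.903 | 3.3% | 89.5% | 91.4% |

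In the third scenario the 95% interval half-width falls by 1.96 × (0.944 − 0.923) = 0.04 mmHg from baseline adjustment and by a further 1.96 × (0.923 − 0.878) = 0.09 mmHg from screening SBP. Entry route (SBP criterion met, yes or no) reduced the residual variance by a further 0.0% in every scenario once both SBP values were in the model.

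At ICC 0.01 the third scenario gives 96.5% with baseline SBP and 98.2% with both, against 95.6% for the change score.

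**The case against.** A reader might infer that every participant has a second SBP occasion which the trial collects and then discards. The documents do not support that. Only the Screening section separates the two surveys. Study population places the qualifying readings within the baseline survey, and two further places speak of screening at baseline. On that reading the screening pair may be the baseline value itself, and nothing is dropped. This objection stands, which is why the screening covariate is conditional. It does not touch the choice between a change score and adjustment for baseline SBP, which arises with one visit or two.

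A reader might also infer that the plan rules out any use of pre-allocation SBP. That is too strong. The adjusted analyses leave their covariates open, and a statistical analysis plan may exist that is not shown. However, those analyses are tied to imbalance and sit beside the main SBP model, and the article does fix the form of that model. A covariate entered only as a main effect would also cancel from the pre-post contrast.

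Thirdly, the gain is small. The village variance supplies 0.45 of the SE² of 0.891 at ICC 0.02 and is left unchanged in these calculations. If nearly everyone enters by SBP, screening SBP adds only about 1-2% of SE. This also stands.

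Finally, the 88.8% might be read as a failed power claim. It lies about one point below the stated level under a simple normal approximation, and is not pressed as a separate point.

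**Conclusion.** The point holds as an optional efficiency improvement. The stated SBP analysis is valid and matches the outcome definition. Regression to the mean after selection on SBP is expected to be equal in both arms, so nothing here biases the comparison.

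At ICC 0.02, power for 3 mmHg rises from 88.8% to about 90-91% with baseline SBP as covariate under mixed entry, or up to about 93% if nearly all enter by SBP. With screening SBP added it is about 91-93%. The SE cut from screening SBP beyond baseline adjustment is about 1-5%. At ICC 0.01 there is little to gain.

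The sizes rest on assumed variance components, an assumed mix of entry routes and an unchanged village variance. The screening part also rests on screening having been a separate occasion.

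**What to change.** First, reconcile the Screening section with the Abstract, Study population and community health worker training sections, so that it is clear whether the screening readings and the baseline-survey readings come from one visit or two.

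Then pre-specify, for SBP, a linear model of follow-up SBP on arm with baseline-survey SBP as covariate, keeping the planned village effect and stratification terms. If screening was a separate occasion, add the mean of the two screening readings as a second covariate. If the pre-post model is kept instead, enter screening SBP through a covariate-by-time term; the power figures above refer to the follow-up model. Do not pool the screening value into the reported baseline, because it is selected at 160 or above for those who enter by SBP. Entry route can be left out.

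The cost is a sentence or two in the analysis plan and, if screening was separate, linking the screening file to the baseline file. No extra measurement is needed. The covariates should be fixed before outcome data are seen by arm.

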### Intervention and control

#### Intervention

The intervention scheme adapts and simplifies international and applicable national clinical guidelines for hypertension and cardiovascular disease management for use by local CHWs to manage cardiovascular high-risk patients in an easily implementable, low cost, and medically effective way
[23, 40]. Local CHWs will be trained to provide basic monthly follow-up care to identified high-risk patients, and refer them to higher level healthcare facilities when necessary. The intervention strategy consists of the following:

#### ‘2 + 2’ intervention model

Taking into consideration the local health behaviors and resources, a simplified management model is devised that focuses on two therapeutic lifestyle recommendations (smoking cessation and salt reduction) and the appropriate prescription of two types of accessible, highly effective, generally safe, and low-cost drugs (blood pressure lowering drugs and aspirin)
[41–46]. In India, as stipulated by the ethic committee, the drugs used in the intervention arm will be also made available to the primary care facilities serving the control villages. Coined the "2 + 2" intervention model, the scheme targets two prevalent risk behaviors with established relationships to CVD while providing instruction on the prescription of two types of basic drugs that have well-documented effects on CVD risk reduction. All individuals in the intervention group will receive therapeutic lifestyle recommendations when applicable, but depending on each individual’s medical situation may be prescribed both, one, or none of the two types of drugs. These interventions will be delivered by CHWs and they will provide monthly follow-up to all high-risk patients under their care.

